#### High-Intensity Interval Training

The exercise intervention will start immediately after the second measurement visit. The HIIT group will follow a HIIT protocol on a cycle ergometer. In detail, the concept of HIIT involves repeated bouts of exercise at an intensity of 85% of W_max4_, interspersed by recovery periods based on a baseline ergospirometry test (Table 1). W_max4_ refers to the hypothetical workload sustainable for 4 minutes [14]. While being hypothetical, W_max4_ is useful for defining the presumably optimal intensity for work intervals at HIIT. The intervention group will perform HIIT sessions involving 5 bouts of 2- to 4-minute work intervals (at 85% of W_max4_) interspersed by 3 minutes of active recovery (at 20% of W_max4_) periods twice per week on nonconsecutive days for 12 weeks. Each work interval will be 2 minutes long in the first week with 5 seconds added to each exercise session (ie, 10 seconds per week) so that HIIT intervals will be 4 minutes long by week 12. If the participant fails to complete the work interval, they will still be instructed to continue the exercise session by starting the following scheduled work intervals after the recovery periods. At the beginning of the intervention period, each HIIT session will last approximately 40 minutes, including a warm-up (at 30% of W_max4_), recovery periods, and a cooldown (at 20% of W_max4_). At the end of the intervention period, each HIIT session will last approximately 50 minutes. HIIT will be conducted in a group of 1 to 4 participants, closely supervised by the KuLTu personnel or students in health sciences adequately trained for the task.

Additionally, an exercise training program will be prescribed for each participant in the HIIT group consisting of home-based low- to moderate-intensity aerobic exercises. An overall weekly goal, including supervised exercise, will be at least 150 to 300 minutes of aerobic exercise, for example, walking, swimming, and cycling (Table 1), following international guidelines [10].

**Table 1. T1:** The exercise training program in the high-intensity interval training group.

Training program characteristics	Study months		
	0‐1	1‐2	2‐3
High-intensity interval training			
Duration of warm-up (min)	5	5	5
High-intensity interval training frequency per week	2	2	2
Intensity of work phase (% W_max4_^a^)	85	85	85
Intensity of recovery phase (% W_max4_)	20	20	20
Interval sets (n)	5	5	5
Duration of the interval (s)	120‐160	160‐200	200‐240
Recovery between sets (min)	3	3	3
Intensity of warm-up (% W_max4_)	30	30	30
Intensity of cooldown (% W_max4_)	20	20	20
Duration of cooldown (min)	5	5	5
Additionally home-based aerobic training			
Duration (min/wk)	150‐300	150‐300	150‐300

a Hypothetical workload sustainable for 4 minutes.

#### AI-Based Coaching for Steady-State Aerobic Training

##### Overview

KuLTu serves as the onsite study center responsible for participant recruitment, baseline and follow-up measurements, supervised HIIT sessions, and the initial setup of study devices and applications. All subsequent participant interaction with the AI system occurs remotely through the mobile app.

The AI-based coaching condition will start immediately after the randomization when participants in this group will be given access to an additional AI coaching feature, unavailable to participants in the other study groups. The clinical trial will use the production version of the AI coach with the addition of a prompt to focus on encouraging moderate, steady-state exercises for 2 to 3 hours per week, also referred to as zone 2 cardio training.

The AI-based coaching feature and its supporting infrastructure are hosted offsite within Oura’s secure cloud environment. Physiological data captured by the Oura Ring are transferred automatically to Oura’s cloud servers via the participant’s smartphone, processed to generate individualized insights, and returned to the participant through the app interface. Oura maintains the offsite computational resources, data storage systems, and model update processes.

The AI coach uses LLMs to provide personalized health behavior coaching for users. The feature will primarily be a chat interface where the user can ask questions about their health data (eg, question: “How were my sleep scores last night?”; answer: “Last night, it seems you had about 7 hours of sleep with some restlessness. Your Sleep Score was 83”) and discuss nonclinical behavior change (eg, question: “I’ve been thinking I’d like to do more stretching”; answer: “Flexibility and mobility are key. Consider focusing on stretches that target the hips, groin, hamstrings, and lower back.”). This creates a feedback loop of observing health data, making behavioral changes, and tracking potential changes. The AI coach will have access to the user’s health data and can create a memory out of things the user tells them about their life and preferences, which the AI coach can use to make nonclinical recommendations to the user that are adapted to their unique personal data, circumstances, and preferences. The user has full access to, and the ability to delete, the memories created by the feature. The foundation model vendor does not have direct access to user data, only through an API, which means that user data cannot be used by the vendor for LLM training.

The coaching content operationalizes a set of established behavior change techniques, described here using the Behavior Change Technique Taxonomy (version 1) [15]. The study-specific configuration applies the following techniques: goal setting and goal review (maintaining or modestly increasing weekly zone 2 volume toward 2‐3 h), problem solving and barrier identification (addressing time constraints and motivation), action planning (eg, shorter or routine-integrated sessions), instruction on how to perform the behavior, information about the health consequences of the behavior, social and emotional support, and self-monitoring with feedback enabled by continuous Oura data. These techniques operationalize core constructs of Social Cognitive Theory, particularly self-efficacy and self-regulation. As these techniques reflect the study-specific layer applied atop the proprietary base model, they are illustrative of the intervention’s behavioral content rather than an exhaustive specification.

##### AI Algorithm Version and Update Management

The AI-based coaching feature used in this trial will be *Oura Advisor*, integrated within the Oura App. Participants will access the frozen production build active between October 2024 and May 2025. During the study period, Oura is expected to release routine updates to the consumer app environment. Engineering records will later be reviewed to determine which of these deployments affect the Advisor component accessible to participants.

All updates are expected to primarily involve interface refinements, bug fixes, or adjustments to data fetch and display systems. No modifications will be made to the underlying LLM weights or to the recommendation algorithms. The prompt configuration governing the Advisor’s behavior will remain fixed throughout the study period. Planned updates may include minor improvements to how data are structured or presented to the model, but such changes will not alter the substantive content or logic of the recommendations.

A version control log will be maintained by Oura’s engineering team. This log will include build identifiers, deployment dates, and a short description of each update’s functional scope.

##### Input Data–Level Inclusion and Exclusion Criteria

The AI-based coaching system processes physiological and behavioral input data generated by the Oura Ring and the Oura App to generate personalized feedback for participants. Data are accepted by the AI system only when sensor and synchronization quality meet predefined thresholds:

PPG and motion signals meet Oura’s internal quality control thresholds (signal quality ≥95% for nightly heart rate variability; adequate wear time ≥20 hours per day on ≥5 days per week);The ring and app remain synchronized via Bluetooth and a cloud connection; andUser-initiated text interactions occur within the study period and in a language supported by the system.

Data are excluded when signal quality is insufficient, the ring is not worn for ≥3 consecutive days, the app is uninstalled, or the participant withdraws consent for data use. These technical criteria ensure that the AI receives input consistent with the data distributions on which the algorithms were developed and validated.

##### Acquisition and Selection of Input Data

Physiological inputs are acquired passively by the Oura Ring, which records PPG, accelerometer, and temperature data. These data are encrypted, transferred via Bluetooth to the participant’s smartphone, and uploaded automatically to Oura’s secure cloud servers. The AI coach accesses processed daily summaries (eg, sleep duration, heart rate variability, resting heart rate, and activity rate) through the same internal data pipeline used for the standard Oura App features. Only validated, successfully uploaded data are accessible to the AI coach; no raw sensor streams are analyzed locally on the phone. In addition, participants may provide voluntary contextual information (eg, preferences, barriers, and exercise intentions) through text chat. These text exchanges are stored in the user’s encrypted account and accessed by the AI for personalization.

##### Handling of Poor Quality or Unavailable Input Data

Data quality assessment is performed automatically within Oura’s cloud infrastructure prior to any AI processing. PPG and motion signals are continuously quality checked; segments that fail to meet internal thresholds (eg, signal quality <95% or missing synchronization for >24 h) are flagged as invalid. When insufficient data are available, the AI coach defaults to generalized guidance based on the user’s recent behavioral trends rather than producing data-specific recommendations. Missing or poor quality periods are surfaced to participants through standard Oura notifications encouraging ring wear or device synchronization. All raw and flagged data remain in the research database for completeness but are excluded from AI-generated personalization.

##### Human-AI Interaction in Input Handling

No manual preprocessing or expert adjudication of physiological data occurs before AI processing; all data selection and quality control are automated within Oura’s pipeline. Human involvement is limited to participant setup and troubleshooting at baseline visits. Participants themselves interact with the AI coach through natural-language chat in plain English. No technical or clinical expertise is required beyond basic smartphone literacy. Research personnel at KuLTu oversee adherence and safety but do not handle raw sensor data or intervene in the AI’s preprocessing.

##### Output of the AI Intervention

The AI coach produces text-based conversational outputs that deliver personalized, nonclinical behavior change guidance. Outputs include daily or weekly motivational messages, reflections on progress, and specific suggestions for moderate, steady-state aerobic exercise (“zone 2” training) based on recent Oura metrics. Responses appear within the in-app chat interface and are visible only to the participant. No diagnostic or prescriptive medical advice is generated. To preserve outcome blinding, the coach is configured not to disclose participants’ CVA or cardiorespiratory fitness. Weight loss and calorie-based framing are excluded, and participants who report a condition such as arrhythmia are advised to follow professional medical guidance before receiving general activity suggestions. No automated alerts are sent to researchers or clinicians.

##### Role of AI Output in Decision-Making

The AI output contributes to participant decision-making by guiding self-directed exercise behavior during the 12-week intervention. Participants may choose to follow or disregard the AI’s suggestions; no clinical decisions or safety monitoring depend on the AI. Research staff and clinicians do not view or act on AI messages. Thus, the AI serves as a behavioral support tool within a preventive health context rather than a component of clinical care.

##### Performance Error Identification

The AI-based coaching feature will operate as a stable, production-level system throughout the intervention period with the addition of the study-specific prompt section, instructing the focus on steady-state cardio. The research team will not perform real-time monitoring or iterative modification of the algorithm or its outputs during the trial. Routine system oversight, including automated logging of software bugs, connectivity issues, and latency events, will be conducted by Oura’s engineering team as part of the company’s standard production maintenance, rather than as a trial-specific activity.

Following completion of the 12-week intervention, Oura and the study team will conduct a retrospective assessment of the Advisor chat performance to identify any technical issues or irregularities that may have affected participant interactions. The retrospective analysis will focus on software reliability, message delivery consistency, and adherence to the intended behavioral support scope. A summary of this evaluation will be included in the final study report.

##### Access to the AI Intervention and Code

The underlying model architecture, prompting framework, and source code will remain confidential and will not be publicly available due to commercial and data security restrictions. The version deployed for this study will be identical to the production version available to Oura Members, with the exception of configuration settings that specify the study’s focus on steady-state aerobic training.

For research transparency, upon reasonable request, Oura may consider providing the investigators with more detailed descriptions summarizing the Advisor’s operational scope. Technical details of any algorithms, data inputs and outputs, quality control mechanisms, and version history for the duration of the study are proprietary material. External access to the AI codebase or model weights will not be granted.

### Statistical Analysis

#### Overview of Statistical Analysis

The statistical analysis for this study will use a comprehensive approach that combines both frequentist and Bayesian frameworks. This dual methodology is chosen due to the inherent challenges of this trial, including the known variability of arterial stiffness and the complexities of adherence to a behavioral intervention. We postulate that relying on a single analytical approach would provide an incomplete picture of the evidence.

For our frequentist analysis, instead of relying on a strict dichotomization of results based on a single *P* value threshold, we will interpret *P* values as a continuous measure of evidence against the null hypothesis. The *P* values will be reported in full, and the strength of the evidence will be discussed in the context with effect sizes, CIs, and the clinical significance of the findings. This approach aligns with modern statistical recommendations that discourage the oversimplification of results into “statistically significant” or “not significant.”

In parallel, we will conduct a Bayesian analysis to provide a more nuanced understanding of our data. This approach allows us to quantify the probability of an effect existing and to incorporate prior knowledge about the intervention’s likely impact. We will specify our priors transparently and, where appropriate, conduct sensitivity analyses to assess the robustness of our conclusions to different prior assumptions. The results from the Bayesian analysis, including posterior probabilities and credible intervals, will complement the frequentist results by offering a more direct assessment of the evidence for or against our hypotheses.

#### Power Calculations

The sample size for this study is based on detecting a change in PWV as measured by the gold-standard reference device (Complior). We also leverage data from the pilot trial. Previous literature has shown that 4 to 8 weeks of aerobic exercise can reduce PWV by −0.35 (−0.68,−0.02) m/s and a 9‐ to 16-week intervention by −0.69 (−1.13, −0.25) m/s [6]. This outcome is heavily dependent on changes in VO_₂_max; for example, a less than 10% improvement will only result in a −0.4 (−0.52,−0.28) m/s change in PWV, whereas >20% improvement will result in a −1.72 (−2.39,−1.04) m/s change. On the basis of the pilot trial, we estimate that the conservative effect (−0.4 m/s) is more realistic, and this is selected as the expected effect size. We also know from the pilot trial that the SD of PWV is quite large relative to the expected effect size. By sampling the pilot data, we obtain an SD of 1.4 m/s for the 30‐ to 65-year-old age group. Using these numbers in standard power calculations [16] results in a required sample size of 193 per group, assuming 80% power at alpha level of .05 (2-sided test). On the basis of pilot, we also know that the correlation between pre- and postintervention PWV measurements in the control group is high (*R*=0.86) and that the correlation is mostly explained by age, sex, BMI, and blood pressure. While the results will be analyzed using a mixed linear model (see below), for which there is no formal power calculation protocol, we leverage the sample size calculations developed by Borm et al [17] for analysis of covariance and adjust the sample size with (1−⍴^2^), where ⍴ is the correlation coefficient for pre- and postintervention outcome variables. This yields a sample size of 50 per group, and to account for attrition, a 10% increase is considered sufficient, leading to a final sample size of 55 per group. A sensitivity analysis illustrates that with a lower-than-expected pre-post correlation (ρ=0.75), the required sample size increases to approximately 94 participants per group (including 10% attrition). On the other hand, with a higher-than-expected pre-post correlation (ρ=0.95), the required sample size decreases to approximately 21 participants per group.

#### Frequentist Analysis Plan

The primary frequentist analysis will be based on the ITT framework, defined as all randomized participants included in the groups to which they were initially assigned, regardless of adherence or withdrawal. The mixed linear model (see below), which inherently accommodates longitudinal data with missing time points under the assumption of missing at random, will be the primary method used to analyze this ITT population. The ITT analysis provides an unbiased estimate of the intervention’s effectiveness under real-world conditions. However, we expect highly motivated participants to engage the most in their assigned interventions and thus receive the most benefit. This will be investigated in mediator analyses. The intervention may work differently for certain people (eg, men vs women), and these will be studied as moderators. Both mediator and moderator analyses are described below.

The difference between the AI group and the Oura Ring only group will be considered the primary comparison, while differences across other group pairs will be exploratory. The primary analysis will be based on a mixed linear model, which is an appropriate method for analyzing repeated measures data while accounting for individual-level variability. This model will be used to assess the effectiveness of the interventions and compare the mean postintervention cfPWV and VO_2_max across the 3 study groups. We will assume that any missing data are missing at rMissing At Random. The results will be presented with full, numeric *P* values, mean differences, and 95% CIs, avoiding an arbitrary (eg, *P*=.05) dichotomy into statistically “significant” and “insignificant.” No formal correction for multiple comparisons will be applied. Instead, we used a linear mixed model, which induces partial pooling of group-level estimates. As discussed by Gelman et al [18], this approach reduces the risk of overestimating spurious differences that can arise from multiple comparisons, thereby mitigating concerns related to multiple testing. Accordingly, we will focus on effect sizes and their uncertainty rather than dichotomous significance testing.

To evaluate how strongly candidate mediators account for the intervention-outcome association, each mediator will be entered sequentially into the previously specified linear mixed model, and the resulting change in the intervention regression coefficients will be examined. The proportion of attenuation attributable to each mediator will be calculated as follows: (1−[regression coefficient adjusted for the mediator/regression coefficient adjusted for the determinant])×100%. In parallel, we will assess the incremental predictive value contributed by the intervention effects beyond their presumed mediators. The mediation analyses will be conducted in the full participant population across all randomization groups.

In addition to mediator analyses, we will evaluate prespecified moderators (eg, sex, age, baseline cfPWV, and cardiorespiratory fitness) by extending the primary linear mixed model to include the group×time×moderator interaction. For binary moderators (eg, sex), inference will focus on the group×time×sex term; for continuous moderators, variables will be mean-centered and effects probed at interpretable values (eg, mean, 1 SD) via model-based marginal means and simple-slope contrasts. When an interaction shows evidence of effect modification, we will present stratified (subgroup) estimates and contrasts within moderator levels for interpretation.

These secondary analyses are crucial for exploring potential effects that may be obscured by the ITT analysis, particularly if adherence is low. They will be clearly identified as exploratory and will complement the primary ITT analysis.

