**Methods:**

This randomized controlled trial will recruit 165 eligible sedentary participants aged 30 to 65 years. The co-primary outcomes, cfPWV and VO_2_max, are measured at baseline and will be repeated after 12 weeks. Participants are equally randomized into 3 groups: an AI-based coaching group (steady-state exercise), an HIIT group (supervised exercise), and a control group (usual low activity). The AI-based coaching group receives personalized guidance using large language model technology. All participants wear the Oura Ring and are blinded to the cardiovascular health metrics provided by the ring.

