#### Bayesian Analysis Plan

In parallel with the frequentist analysis, we will conduct a Bayesian analysis for the primary and key secondary outcomes (cfPWV and VO_₂_max change). The Bayesian model will mirror the mixed linear model used in the frequentist framework to ensure direct comparability of results; specifically, we will include a random intercept at the individual level, fixed effects for the 3 treatment groups, and covariate adjustment for baseline outcome, age, sex, BMI, and systolic blood pressure. By aligning the model structure, any differences between approaches will reflect the inferential framework (use of priors and posterior probabilities) rather than the model specification.

Priors will be specified transparently and chosen to balance prior knowledge with appropriate uncertainty. For the primary treatment effect on cfPWV, we will use a normal prior with a mean of −0.4 m/s and an SD of 0.5 m/s, centered on our expectation derived from an unpublished pilot study, while allowing the posterior to span both benefit and no effect. For VO_₂_max, we will use a weakly informative normal prior with a mean of 0 and an SD of 5 mL/kg/min, covering plausible changes of −10 to 10 mL/kg/min changes. Covariate effects will receive normal(0, 10) priors to mirror the unpenalized adjustments in the frequentist model. Variance parameters, including the SDs of the individual random intercepts and the residual error, will be given half-Normal(0, 5) priors to provide mild regularization of variability estimates.

The likelihood assumes normally distributed postintervention outcomes with participant-specific random intercepts and a common residual variance. We will sample from the joint posterior distribution of all parameters and assess convergence using split-chain diagnostics (eg, agreement across chains) alongside effective sample size thresholds to ensure stable estimation. Posterior summaries will be presented as means and 95% credible intervals for each treatment contrast (AI vs control; HIIT vs control; and AI vs HIIT), providing directly interpretable intervals for the magnitude and direction of the effects.

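### Multiplicity correction is waived on the ground of partial pooling, which the specified model does not do, and the rank and joint reading of the two primary outcomes are left unsettled

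*Protocol article*

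**What the plan says.** In the Frequentist Analysis Plan the protocol article states "No formal correction for multiple comparisons will be applied" and continues: "Instead, we used a linear mixed model, which induces partial pooling of group-level estimates". It then argues that this lowers the risk of overstating chance differences and so eases the multiple-testing problem. The reporting stance that follows, effect sizes with their uncertainty, is presented as a consequence.

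The model itself is written out only in the Bayesian Analysis Plan: "we will include a random intercept at the individual level, fixed effects for the 3 treatment groups, and covariate adjustment for baseline outcome", along with age, sex, BMI and systolic blood pressure. The link to the frequentist model is explicit: "The Bayesian model will mirror the mixed linear model used in the frequentist framework to ensure direct comparability of results".

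On the outcomes, the Abstract says "The co-primary outcomes, cfPWV and VO_2_max, are measured at baseline", and the Introduction likewise names the 12-week changes in both as primary. The Bayesian Analysis Plan instead says "we will conduct a Bayesian analysis for the primary and key secondary outcomes" and lists the same two, cfPWV and VO2max change, in brackets. Power Calculations sizes the trial on cfPWV alone at two-sided .05. The Results section says that no separate analysis plan is currently planned because this document holds the necessary detail.

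**The concern.** Partial pooling is a property of effects modelled as draws from a common distribution: each estimate is pulled towards the common mean by an amount set by the estimated variance. Fixed effects are not treated in this way. If group is fixed, the reason given for leaving out a correction describes a different model from the one to be fitted.

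This bears on what the trial may claim. A reader who accepts the sentence would take a favourable result on one of the two primary outcomes as already tempered by the model. The unsettled rank of VO2max adds to this: if only one outcome is favourable, the document does not tell a reader in advance whether that is a primary finding, a secondary finding or a mixed result. The plan says that it is meant to limit selective reporting, and this is the place where that aim needs a stated rule.

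**Working it through.** **1. The plan's own figure.** Inputs from Power Calculations: difference 0.4 m/s, SD 1.4 m/s, two-sided alpha .05, power 80%, pre-post correlation 0.86.
- Unadjusted: n = 2(1.960 + 0.842)² × 1.4²/0.4² = 192.3, rounded up to 193 per group, as stated.
- With the covariance factor: 193 × (1 − 0.86²) = 193 × 0.2604 = 50.3, stated as 50.
- With 10% added: 50 × 1.1 = 55, as stated.

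The sample size reproduces and is not at fault. It uses the full .05 for cfPWV.

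**2. Is anything pooled across groups?** The specified random term is the participant intercept, and group is fixed. The Frequentist Analysis Plan fits this reading: its mediator and moderator analyses work with intervention regression coefficients and group-by-time interactions, and it mentions no random group effect. As a check, 60 three-arm pre/post data sets were simulated (50 per arm, correlation 0.86) and fitted by REML with a random participant intercept and fixed group × time. The AI-versus-control estimate equalled the raw difference in mean change in every data set, with a largest discrepancy of about 9 × 10⁻¹⁵. There was no shrinkage. In 20,000 simulated null trials at each of three correlations, using t tests of the fixed contrasts, the type I error per outcome stayed at about .05.

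**3. Is anything pooled across outcomes?** No joint model of cfPWV and VO2max is described. Even random group effects within each outcome's model would not link the two.

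**4. Do the Bayesian priors supply the protection?** With 50 evaluable per group, SE = 1.4 × √0.2604 × √(2/50) = 0.143 m/s, so SE² = 0.0204.
- Main cfPWV prior (mean −0.4, SD 0.5): prior weight 0.0204/(0.0204 + 0.25) = 8%. An estimate of 0 moves to about −0.03, and an estimate of −0.6 moves to about −0.585. The pull is towards −0.4, not towards no effect.
- Skeptical prior (mean 0, SD 0.3): prior weight 0.0204/(0.0204 + 0.09) = 18%, towards zero. This is a sensitivity analysis, for cfPWV only.
- VO2max prior (mean 0, SD 5 mL/kg/min): centred on zero, and described by the plan as weakly informative.

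None of these acts on the frequentist P values and intervals, which is where the pooling argument is made.

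**5. Error rate for the primary comparison, AI versus Oura Ring only.** Assume that P<.05 on either outcome could support a claim. The correlation between the two test statistics is not given, so a range is shown.

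| Assumed correlation | Chance of at least one false positive |
|---|---|
| 0 | 1 − 0.95² = 9.75% |
| 0.3 | 9.5% |
| 0.5 | 9.1% |
| 0.7 | 8.3% |
| 0.9 | 7.0% |

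The simulated null trials gave 9.8%, 9.2% and 9.1% at correlations 0, 0.3 and 0.5. If both outcomes must be favourable, the rate does not exceed 5%.

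**6. Price of one possible correction.** With alpha halved to .025 and 50 evaluable per group, cfPWV power is Φ(0.4/0.143 − 2.241) = 71%, against Φ(0.4/0.143 − 1.960) = 80% at .05. Restoring 80% would take 233 × 0.2604 = 60.7, that is 61 evaluable per group. A fixed sequence with cfPWV first costs cfPWV no power.

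**The case against.** The strongest defence is that the plan does not need the pooling sentence. Overview of Statistical Analysis treats P values as graded evidence, calls all conclusions exploratory and declines single-threshold rules. The Frequentist Analysis Plan names one primary comparison and reports full P values with 95% CIs. That is a separate and defensible reason for not correcting, and deleting the sentence would leave every planned estimate unchanged. This stands: the absence of a correction is not in itself the defect. It does not make the technical claim true, however, and it does not settle the rank of VO2max.

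It can also be said that the fixed-effect wording sits in the Bayesian section. That is so, but the plan says that the two models share one structure, and no other specification is given.

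Four stronger readings are tempting, and the documents do not support them.
- A reader might infer that the error rate of the trial is nearly 10%. That needs an either-outcome rule at P<.05, which is stated nowhere.
- A reader might count all three group pairs on both outcomes and reach 21% to 23%. Four of those six tests are between pairs that the plan already labels exploratory.
- A reader might infer that the Bayesian analysis shrinks only away from the null. The skeptical prior and the VO2max prior are both centred on zero, and the main cfPWV prior pulls estimates beyond −0.4 back towards it.
- A reader might infer that VO2max has to be demoted. In an ongoing trial that is a trade-off for the sponsor, and a mistaken sentence does not compel it.

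**Conclusion.** The stated reason for omitting a correction is wrong for the model that the plan specifies: treatment contrasts are not pooled across groups, and nothing is pooled across the two outcomes. The status of VO2max is inconsistent between the Abstract and Introduction on one side and the Bayesian Analysis Plan on the other, and no rule for reading the two outcomes together is given.

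The size depends on that missing rule. Under an either-outcome reading at two-sided P<.05, the false-positive chance for AI versus control is about 9.1% to 9.75% at assumed correlations of 0.5 to 0. Under a both-required reading there is no inflation. The conclusion on pooling rests on the statement that the frequentist model has the same structure as the Bayesian one. This should be fixed, but it does not undermine the design or the sample size.

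**What to change.** - Delete the partial-pooling sentence and the claim that it mitigates multiple testing.
- Give VO2max one status, and use it in the Abstract, the Introduction and the Bayesian Analysis Plan.
- State, before the group codes are released to the analysts, how the two outcomes are read together. The options are: both required; cfPWV first in fixed sequence, which fits a sample size based on cfPWV; or Holm-adjusted P values or 97.5% CIs reported alongside the planned ones. The fixed sequence needs a threshold that the plan otherwise avoids. Adjusted P values can be reported as numbers without one.
- If no correction is kept, rest this openly on the exploratory, no-threshold stance, and say that results for the two primary outcomes are unadjusted.

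Cost: a wording change. If outcome status or analysis changes, Ethical Considerations commits the investigators to inform both the ethics committee and the registry and to report the change in the final study report. The scientific cost is a possibly weaker claim when only one outcome is favourable. If alpha is split, cfPWV power falls from 80% to about 71%.
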